**Protocol Summary**

| **Short Title** | Postoperative Elbow rehabilitation |
| --- | --- |
| **Objectives** | This study aims to assess the efficacy of WeChat–based plus scene–graphics health education following open elbow arthrolysis. |
| **Study Design** | This study is a single-center, interventional, historical control study. |
| **Ethical Registration Number** | 2020–028 |
| **Clinical Research Registration Number** | ChiCTR2000036004 |
| **Study Center** | Shanghai sixth people’s hospital, China Shanghai |
| **Primary Outcome** | The primary outcome was the difference in elbow range of motion after 1-week, 6-weeks and 12-weeks post-operative. |
| **Secondary Outcome** | 1-week, 6-weeks and 12-weeks of Psysiological function in quality-of-life scores(SF-36), elbow function by using Mayo Elbow Performance Score(MEPS), assessing the incidence of complications through clinic manifestations and examination results. |
| **Population** | 112 patients diagnosed as elbow stiffness that need to undergo open elbow arthrolysis will be recruited and enrolled into the WeChat group (n=56) or the Control group (n=56). |
| **Study Duration** | 15 months |
| **Follow-up visit** | 1-week, 6-weeks and 12-weeks post-operative |
| **Intervention Group** | Received health education using WeChat and scene–graphics. The information in 4-part comics was shared via a WeChat public account. The patients got information from the account and had daily lessons during hospitalization, and online instruction in a WeChat group after discharge until 12 weeks post-operation. |
| **Control Group** | traditional health education  Received the usual health education provided by the hospital, which includes verbal instructions and electronic materials. Patients in this group did not receive any WeChat-based or scene-graphics education. |
| **Main Inclusion Criteria** | 1. Patients must be aged >18 years old.  2. Must have a diagnosis of elbow stiffness requiring surgical intervention.  3. Must be willing and able to provide informed consent.  4. Must be able to understand and communicate in Mandarin, as the WeChat public account and group will be conducted in these languages.  5. Must have access to a smartphone with WeChat application installed for the intervention group participants. |

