| **Main Exclusion Criteria** | 1. Patients with a history of psychiatric disorders or cognitive impairments that would interfere with the ability to comply with the study protocol.  2. Patients who have undergone previous elbow surgeries or have other medical conditions that could affect elbow function.  3. Pregnant women or those planning to become pregnant during the study period.  4. Individuals with known allergies to any of the medications or materials used during the surgical procedure.  5. Patients who are participating in other clinical trials simultaneously or have done so within the past 6 months. |
| **Allocation** | Eligible patients were split into two groups by admission time: the control group (56 patients enrolled from Jan.–Jun. 2021) and the WeChat group (56 patients enrolled from Jul.–Dec. 2021). |
| **Statistical Methodology** | The statistical analysis was conducted using SPSS software version 26.0. The primary outcome measures were elbow range of motion (ROM), which were assessed at baseline, at discharge, and at 1, 6, and 12 weeks post-operation. Secondary outcomes included quality of life, elbow function, and postoperative complications. The data was analyzed using descriptive statistics to summarize the demographic and clinical characteristics of the participants. Inferential statistics, including t-tests for continuous variables and chi-square tests for categorical variables, were used to compare the differences between the control and WeChat groups. Repeated measures analysis of variance (ANOVA) was conducted to evaluate the changes in ROM over time within each group and between the groups. The significance level was set at p<0.05 for all statistical tests. |
| **Safety** | Adverse events will be summarized for each group. The safety analysis will focus on the frequency and severity of any complications that arise during the study period. This includes, but is not limited to, infections, allergic reactions, and any other unexpected medical events that may occur. The safety data will be analyzed to determine if there is a significant difference in the incidence of adverse events between the control and WeChat groups. The results will be reported in accordance with the CONSORT guidelines for randomized controlled trials, ensuring transparency and completeness of the safety data. |

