According to incomplete yet telling statistics, the situation is quite concerning. The incidence of postoperative elbow issues stands at a staggering 56 - 87% [5]. The probability of renewed elbow stiffness is also alarmingly high, ranging from 8.4 - 47% [5, 6]. Furthermore, the rate of secondary surgery, which is often required to address these complications, is between 10 - 34% [6, 7]. To make matters worse, the rate of patient dissatisfaction due to these issues reaches 21% [7]. These figures clearly emphasize the need to enhance the precision of postoperative rehabilitation and ensure better patient adherence to the rehabilitation protocols.Nevertheless, achieving perfect postoperative rehabilitation is an extremely challenging task. This is primarily because the process is not only prolonged but also highly intricate [6, 12, 13]. Standard postoperative rehabilitation typically spans a period of one year and is systematically divided into three distinct phases [6, 14, 15]. The first phase, known as the acute phase, commences on the very first day after the surgery and extends up to 6 weeks. During this initial and crucial period, the rehabilitation process involves a series of passive, assisted, and active elbow flexion and extension motions [6, 14, 15]. To be more specific, on the first day, patients are recommended to start with 30 such movements. As the days progress, this number is increased by 30 each day until a total of 300 movements are achieved on a daily basis [6, 14]. The second phase, which lasts from 6 weeks to 3 months after the surgery, is designated as the subacute phase. During this period, the daily requirement for these elbow movements remains at 300, ensuring a consistent and continuous rehabilitation effort [14].The third and final phase, the functional phase, lasts from 3 months up to one year after the operation. This phase is particularly significant as it involves the addition of weight - bearing practices to the rehabilitation routine. Moreover, the intensity of the rehabilitation activities is gradually increased on a daily basis during this period [14, 15].It is important to recognize that in addition to the initial rehabilitation process that takes place within the hospital environment, patients are also required to continue their rehabilitation efforts at home. This home - based rehabilitation is an integral part of the overall recovery process. As a result, having a comprehensive and highly accurate grasp of the relevant knowledge related to rehabilitation is absolutely crucial for ensuring effective rehabilitation outcomes [13, 14, 16].

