**4.4.3 Statistical Method**

SPSS Statistics version 26.0 (IBM Corp) was utilized for the data analysis. The chi-square test was used to analyze sex, disease side, and the incidence of postoperative complications. The collected data were subjected to a comprehensive statistical analysis to evaluate the effectiveness of the intervention on elbow stiffness. The normality of the data was first assessed using the Shapiro-Wilk test. For variables that satisfied the normality test, parametric statistical methods were employed, including the paired sample t-test for comparing pre-intervention and post-intervention values. For variables that did not meet the normality assumption, non-parametric tests, specifically the Wilcoxon signed-rank test, were utilized. The changes in elbow range of motion (ROM), the Mayo Elbow Performance Score (MEPS), and the Short Form-36 (SF-36) health survey scores at each time point were analyzed using repeated measures analyses of variance (ANOVA). The results were presented as mean ± standard deviation (SD) for continuous variables and as frequencies and percentages for categorical variables. In cases where the data were not normally distributed, median values and interquartile ranges (IQRs) were reported. The level of statistical significance was set at a two-tailed P value < .05. All statistical analyses were performed using appropriate software to ensure accuracy and to provide a robust interpretation of the study findings.

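### The only between-arm inference planned for adverse events and complications is a yes/no significance test on 56 versus 56 patients, which leaves the uncertainty of the difference unquantified

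*Protocol*

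**What the plan says.** - **Safety row, Protocol Summary.** The between-arm question is posed as a test: "The safety data will be analyzed to determine if there is a significant difference in the incidence of adverse events between the control and WeChat". This row also plans description: "Adverse events will be summarized for each group". It then sets the emphasis: "The safety analysis will focus on the frequency and severity of any complications that arise during the study period".
- **Section 4.4.3.** The test is named: "The chi-square test was used to analyze sex, disease side, and the incidence of postoperative complications". The level is given as well: "The level of statistical significance was set at a two-tailed P value < .05". Categorical variables are presented as frequencies and percentages.
- **Statistical Methodology row, Protocol Summary.** "The significance level was set at p<0.05 for all statistical tests".
- **Population row, Protocol Summary.** Patients are "enrolled into the WeChat group (n=56) or the Control group (n=56").
- **Section 2.2.1.** The aim for complications is a reduction.
- **Result row, Protocol Summary.** Each efficacy outcome (four angles, the elbow score and SF-36) has a between-group difference with a 95% confidence interval. Complications, a listed secondary outcome, do not appear there.

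**The concern.** A test of whether incidence differs significantly has two outputs. With 56 patients per arm and binary events, the second output, not significant, is compatible both with no relevant difference and with a sizeable one seen in too few events. Percentages per arm do not tell the reader which of these applies, and the protocol provides nothing that does.

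Two conclusions are exposed. One is harm: sections 6.3.1 and 6.3.2 treat new heterotopic ossification and worsening nerve symptoms as things that can emerge during rehabilitation, and the intervention adds motion instruction and exercise check-ins. The other is benefit: the same test judges the reduction in complications sought in section 2.2.1, so a real reduction could be passed over as easily as a real increase. Binary complications carry less information per patient than the angles and scores, yet they are the outcomes left without an interval.

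**Working it through.** **Inputs from the protocol.** n = 56 per arm; two-sided alpha 0.05; chi-square test. For a background rate, section 1.1 says: "The probability of renewed elbow stiffness is also alarmingly high, ranging from 8.4 - 47% [5, 6"].

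**Assumptions.** The protocol gives no expected complication rate for its own control arm, and no power or sample-size calculation for safety, so there is no planned figure to reproduce. Control rates of 8.4% and 47% are the ends of the quoted range. The 5% rate stands for rarer events and is assumed. The other rates are illustrative.

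**Step 1: probability of missing a true difference.** Let X and Y be independent Binomial(56, p) and Binomial(56, q). For each of the 57 × 57 tables the statistic is

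chi² = N·d² / (n²·s·(N − s)), with N = 112, n = 56, s = x + y, d = |x(n − y) − y(n − x)|.

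The continuity-corrected form replaces d by max(0, d − N/2). The miss probability is the total probability of tables with chi² below 3.84.

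| Control rate to WeChat rate | Missed, Pearson | Missed, continuity-corrected |
|---|---|---|
| *Doubling* | | |
| 5% to 10% | 0.838 | 0.922 |
| 8.4% to 16.8% | 0.735 | 0.824 |
| 10% to 20% | 0.683 | 0.775 |
| 15% to 30% | 0.514 | 0.606 |
| 16% to 32% | 0.482 | 0.569 |
| 18% to 36% | 0.418 | 0.498 |
| 20% to 40% | 0.351 | 0.427 |
| 25% to 50% | 0.211 | 0.268 |
| 34% to 68% | 0.045 | 0.066 |
| 47% to 94% | 0.000 | 0.000 |
| *Increase of 10 points* | | |
| 8.4% to 18.4% | 0.658 | 0.758 |
| 20% to 30% | 0.768 | 0.828 |
| 47% to 57% | 0.823 | 0.868 |

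Fisher's exact test agrees with the corrected column to three decimals for the doublings. The miss probability for a doubling passes one half at a control rate of about 16% (Pearson) or 18% (corrected).

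**Step 2: what can be detected.** With the Pearson test, 80% power is reached at 28.2% from a control rate of 8.4% (19.8 points), and at 72.9% from 47% (25.9 points).

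**Step 3: the benefit direction.** Halving from 20% to 10% is the 10% versus 20% comparison reversed, so it is missed with probability 0.683 (0.775 corrected).

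**Step 4: what an interval adds.** Take 5/56 control events and 11/56 WeChat events.

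- d = 11 × 51 − 5 × 45 = 336
- chi² = 112 × 336² / (56² × 16 × 96) = 2.625, p = 0.105 (0.177 corrected): not significant
- Risk difference = 0.1964 − 0.0893 = 0.1071
- Wilson limits: 0.1134 to 0.3184 for 11/56; 0.0387 to 0.1926 for 5/56
- Newcombe lower limit = 0.1071 − √[(0.1964 − 0.1134)² + (0.1926 − 0.0893)²] = −0.025
- Newcombe upper limit = 0.1071 + √[(0.3184 − 0.1964)² + (0.0893 − 0.0387)²] = 0.239

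The test says not significant; the interval says the data are compatible with anything from 2.5 points fewer to 23.9 points more.

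**Step 5: expected precision.** With equal true rates, the approximate half-width is 1.96·√(2p(1 − p)/56): 10.3 points at 8.4%, 14.8 at 20% and 18.5 at 47%.

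**The case against.** Several stronger readings are tempting, and the protocol does not support them.

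- **That a doubling would usually be missed.** This depends on the control rate. Within the protocol's own range for renewed stiffness, a doubling from 25% is detected about 79% of the time, from 34% about 96%, and from 47% practically always. The 56–87% quoted in section 1.1 for postoperative elbow issues cannot double at all. The claim holds only for events below about 16–18%.
- **That safety is judged by the test alone.** The Safety row also promises per-group summaries and attention to frequency and severity, so a reader would see 5/56 and 11/56. This stands, but those summaries do not express the uncertainty of the difference.
- **That a non-significant result will be reported as no difference.** A reader might infer this, but no section says so. The protocol gives no reading of a null result, right or wrong.
- **That a safety margin is missing.** The stated aim is a reduction and no claim of being no worse is planned, so none is required.

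It can also be said that interval methods for safety tables belong in a statistical analysis plan, which is not at hand, and that a chi-square test is a legitimate choice for a binary outcome. Both are fair: the absence of an interval method alone would not be a finding. What remains is that the protocol itself frames the safety question as one of significance.

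Finally, the protocol's premise points towards benefit: section 1.1 links these complications to inadequate rehabilitation, and section 4.3.1 says the educational content was shared with the control arm. That makes harm less expected, but the test is equally weak at showing benefit.

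**Conclusion.** The point holds in limited form, as an inexpensive improvement rather than an error that undermines the trial. The sole inferential criterion between arms for adverse events and complications is significance at 0.05 with 56 per arm. That criterion misses a doubling more often than not for control rates below about 16% (18% corrected), and misses a 10-point increase 66% to 82% of the time at the three control rates checked across the quoted range. A non-significant result therefore cannot carry a statement of equal safety or of no benefit.

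The sizes rest on independent binomial counts, all 56 patients per arm being evaluable, and control rates that the protocol does not fix for its own patients.

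**What to change.** In the Safety row and in section 4.4.3, replace the aim of finding out whether a significant difference exists with estimation:

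1. For each complication, and for any complication, report counts per arm and the WeChat-minus-control risk difference with a two-sided 95% confidence interval, for example Newcombe's. The chi-square p-value may stay beside it.
2. State that p>0.05 will not be taken as evidence of equal safety or of no effect on complications.
3. State that the interval covers sampling error only. The arms are consecutive admission cohorts (January–June and July–December 2021) and section 4.2 says there was no blinding, so the interval does not account for differences between periods or in assessment.

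No margin needs to be added while no claim of being no worse is made.

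The cost is wording in two places and a calculation from counts the study already records, with no extra patients or visits. The downside is a more cautious safety statement, because the intervals will be wide.

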**4.3.1WeChat group**

1. **A Multidisciplinary Team - based WeChat Health Education Program for Elbow Rehabilitation Intervention**

The multidisciplinary team comprised a surgeon, a nurse manager, a rehabilitation therapist, a platform maintenance specialist, and three elbow joint nurse specialists. Together, they developed a comprehensive health education program. The surgeon was responsible for overseeing the intervention, training team members, and evaluating patients' elbow function. The nurse manager ensured the successful implementation of the intervention, while the rehabilitation therapist created content for elbow rehabilitation and provided instructions on performing the necessary exercises. The three nurse specialists were tasked with delivering the health education.

The platform maintenance specialist was in charge of managing the WeChat group, ensuring its smooth operation, and addressing any technical issues that arose. The group was designed to be interactive, allowing participants to ask questions, share experiences, and receive feedback from the medical professionals involved. This setup aimed to enhance participant engagement and adherence to the intervention program.

The WeChat-based health education program was designed to be user-friendly and accessible, with content tailored to the specific needs of elbow rehabilitation. It included educational materials to reinforce learning and encourage self-management of rehabilitation exercises. The program also incorporated a feature for participants to track their progress and set reminders for their daily exercises, which was intended to promote consistency and accountability.

Throughout the intervention, the multidisciplinary team monitored participant activity within the WeChat group, providing encouragement and answering questions to keep participants motivated and informed. The team also used the group to distribute timely updates on the intervention protocol and to remind participants of upcoming training sessions or support line availability. This approach was designed to maximize the effectiveness of the intervention by fostering a supportive community and ensuring that participants felt supported throughout their rehabilitation journey.

(2)T**he creation, pilot study, and application of a comic book for elbow rehabilitation education in an intervention group with the support of a WeChat group.**

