**Process 1: Rehabilitation check-in.**

Patients were contacted periodically to assess their progress and address any challenges they might be facing with their rehabilitation exercises. This follow-up was conducted via WeChat. The nurse reviewed the recorded exercise sessions and provided constructive feedback, offering encouragement and making adjustments to the exercise regimen as necessary. This ongoing support was instrumental in maintaining patient motivation and ensuring that they adhered to their rehabilitation plan, which was critical for their long-term recovery and independence.

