**The processes above were continuous monitoring and feedback by research team.**

To ensure that the rehabilitation process was effective and that patients were progressing as expected, the research nurse implemented a continuous monitoring system. This involved regular check-ins with patients to assess their progress and to identify any challenges they might be facing. The feedback from these sessions was critical in adjusting the rehabilitation plan to better suit the individual needs of each patient. The team also used a feedback loop to incorporate patient suggestions into the program, making it more patient-centered and responsive to their needs. This iterative approach allowed for a dynamic and adaptive rehabilitation process that could evolve with the patient's changing circumstances and recovery milestones.

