**4.3.2 Control group**

The control group received traditional health education. Patients were instructed to access an online manual titled 'Elbow Rehabilitation' by scanning a code using WeChat. The manual provided comprehensive information on elbow anatomy, common injuries, and rehabilitation exercises. It was designed to be user-friendly, with clear illustrations and step-by-step instructions to guide patients through their recovery at home. The control group's approach was more self-directed, with less personal interaction compared to the WeChat group, which received the additional support and resources described earlier.

Post-discharge, weekly follow - up calls were made to ensure the continuity of the recovery process. This group's progress was monitored through periodic phone calls, where they were asked to report on their symptoms and adherence to the rehabilitation exercises. The research team used this information to evaluate the effectiveness of the online manual and self-directed approach.

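### The adverse-event comparison mixes safety with detection, because the two successive cohorts were followed differently between the shared visits

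*Protocol*

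**What the plan says.** The Safety row of the Protocol Summary will "determine if there is a significant difference in the incidence of adverse events between the control and WeChat groups". The scope is open: "This includes, but is not limited to, infections, allergic reactions, and any other unexpected medical events that may occur". The groups are not concurrent: "Eligible patients were split into two groups by admission time", with 56 controls from January to June 2021 and 56 WeChat patients from July to December 2021.

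Contact between visits is described separately for each cohort.

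- **Control (4.3.2):** after discharge, "weekly follow - up calls were made to ensure the continuity of the recovery process". The same section adds: "This group's progress was monitored through periodic phone calls, where they were asked to report on their symptoms and adherence to the rehabilitation exercises". It also says that this group had less personal interaction than the WeChat group.
- **WeChat (4.3.1 and its after-discharge processes):** "the multidisciplinary team monitored participant activity within the WeChat group". At the check-in step, "The nurse reviewed the recorded exercise sessions and provided constructive feedback". One-to-one consultations were available, and "the research nurse implemented a continuous monitoring system", which is explained as regular check-ins.

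Both cohorts share the visits at 1, 6 and 12 weeks, the standardised forms (4.4.1, 5.1), a support line (4.3), and a general statement that all subjects were monitored for distress or complications (3.4). Section 4 says that every participant received equal care and attention. Section 4.4.3 applies a chi-square test to postoperative complications, at a two-sided 5% level.

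**The concern.** An adverse event counts only if someone learns of it. Common forms standardise how an event is written down, not how often anyone looks or asks. The Safety row does not confine the comparison to the shared visits, and it does not separate events by how they came to light. Where one cohort has more channels through which a minor infection, a rash or another unexpected event can reach the team, its recorded rate can be higher with no difference in safety.

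Two errors are possible: the WeChat programme could appear to cause events that it merely uncovered, or a real reduction could go unseen. The second matters because section 2.2.1 places a lower complication rate within the primary purpose. Analysis by a statistician unaware of allocation (4.2) does not help, since events that were never recorded cannot be recovered at analysis.

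**Working it through.** **The plan's own figure.** The protocol gives no expected adverse-event rate, detection rate or power for this comparison, so there is nothing to reproduce. The true rates and capture probabilities below are assumptions, shown over a range.

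**Inputs from the protocol.** 56 per group (Allocation row); two-sided 5% level and chi-square test (4.4.3). The Safety row names no test; I take chi-square because the Statistical Methodology row uses it for categorical variables.

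**Model.** Recorded rate = true rate × probability of capture. The rejection probability is the exact binomial sum over all 57 × 57 possible outcomes of the Pearson chi-square test without continuity correction.

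**Step 1: no true difference, true rate 20% in both cohorts.**

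| Capture, WeChat v control | Recorded rates | Bias | Rejection probability |
|---|---|---|---|
| 90% v 90% | 0.20 × 0.90 = 18% v 18% | 0 points | 5.1% |
| 90% v 80% | 18% v 0.20 × 0.80 = 16% | 2 points | 6.0% |
| 90% v 70% | 18% v 0.20 × 0.70 = 14% | 4 points | 8.9% |
| 90% v 60% | 18% v 0.20 × 0.60 = 12% | 6 points | 14.3% |

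In the last row nearly all rejections (14.0 of the 14.3 percentage points) show more events under WeChat. The recorded rate ratio is 0.90/0.60 = 1.50, although the true ratio is 1.

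**Step 2: dependence on the true rate.** For 90% v 60%, rejection is 8.7% at a true rate of 10% and 28.7% at 40%. For 90% v 70%, it is 6.5% and 15.1%. With equal 90% capture it stays between 4.7% and 5.1% for true rates from 10% to 56%.

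**Step 3: masking.** Let the true WeChat/control ratio be 0.70 and the control rate 40%, so the WeChat rate is 0.70 × 0.40 = 28%.

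- Equal 90% capture: recorded 0.28 × 0.90 = 25.2% v 0.40 × 0.90 = 36%; rejection 24%.
- Capture 90% v 63%: recorded 25.2% v 0.40 × 0.63 = 25.2%; rejection 5%. The benefit has vanished from the data.

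**Step 4: which events are exposed.** The model applies most to events that arise, and perhaps resolve, between visits. Heterotopic ossification, ulnar nerve symptoms and repeat stiffness (4.4.1.2) rest on clinical examination by surgeons on a schedule common to both cohorts, so their capture should differ much less.

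**The case against.** The strongest reply is that the gap in surveillance may be small. The continuous monitoring system is defined only as regular check-ins of unstated frequency, and the after-discharge check-in is described as periodic contact. Weekly calls that ask about symptoms are fairly close follow-up. The support line, the three visits and the general monitoring statement apply to both cohorts. Under mild assumptions (90% v 80%) rejection is 6.0% against a nominal 5%. This stands as a limit on size: control capture near 60% is towards the pessimistic end.

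A reader might infer that a weekly call catches only events still present that day, so that a three-day event is found with probability 3/7 = 43%, against almost certain capture under daily contact. The documents do not support this. Daily lessons belong to the hospital stay, no daily contact after discharge is specified, and a patient asked about symptoms can report something that happened earlier in the week.

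The direction can also be questioned. The control calls explicitly ask about symptoms, while the WeChat text speaks of progress, challenges and exercise technique. More contact is not necessarily more questioning about events. More recorded events under WeChat is therefore the plausible direction, not a demonstrated one.

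Finally, the chi-square test in 4.4.3 is aimed at the surgeon-examined complications, which are little affected. That is fair, but the Safety row sets a wider between-group comparison of its own, and none of the shared arrangements makes detection equal for it.

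**Conclusion.** The point holds for the open-ended adverse events of the Safety row. Their recorded rates combine safety with detection, and the protocol itself describes unequal contact. With a true rate of 20% in both cohorts, the distortion is about 2 points at 90% v 80% capture and 6 points, with about 14% false rejection, at 90% v 60%. These capture figures are assumptions, and the real size cannot be derived from the documents.

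A reader might go further and conclude that no result of this test can be interpreted. That is too strong. If WeChat patients were indeed watched more closely, a significantly lower WeChat rate would be informative despite the bias. The supportable statement is that the all-event comparison is not a comparison of safety alone. The concern is weaker for heterotopic ossification, ulnar nerve symptoms and repeat stiffness.

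**What to change.** In the Safety row and in 4.4.3:

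1. Base the between-group test on events ascertained at the common 1-, 6- and 12-week assessments, with the same form and the same question in both cohorts. The question should cover the whole interval since the last visit, so that resolved events are not lost.
2. Report all other events by group and by source (phone call, WeChat contact, support line), descriptively and without a P value. The Result row of the Summary already gives outcomes, so where collection is over, the source has to come from existing records.
3. State that the all-event comparison is not a comparison of safety alone.
4. Reconcile the equal-attention statement in section 4 with 4.3.2, which says that controls had less personal interaction.

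The cost is a few sentences and a source classification, with retrospective record review if the source was not captured. The tested comparison will contain fewer events, because some between-visit events become descriptive. If existing records cannot show that the visit question covered the interval in both cohorts, that should be stated as a limitation. Confounding by calendar period and unblinded assessment remain after this change.
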